***Criminal justice activities***			
Specific crimes	Criminal records & CLAF	McCollister et al. (2010): direct costs	McCollister et al. (2010): societal costs
Probation visits	CLAF	BLS	BLS
***Other resources***			
Work	NMOS	N/A	Self-reported wages & hours worked
Education	NMOS	N/A	Self-reported time in school & Card (1999) estimates
Participant time	NMOS	N/A	Self-reported or federal minimum wage
Participant travel	Site visit	N/A	Area public transportation fees & IRS mileage rates

*NMOS* Non-study Medical and Other Services form, *T-MSIS* Transformed Medicaid Statistical Information System, *DATCAP* Drug Abuse Treatment Cost Analysis Program instrument, *FSS* Department of Veterans Affairs Federal Supply Schedule, *CLAF* Criminal and Legal Activities Form, *Medicare FFS* Medicare fee-for-service

The societal perspective should account for the “actual value” of all resources associated with the intervention [37]. Thus, Medicare fee-for-service payments will be used to value healthcare resources utilized from the societal perspective, as these payments are designed to reimburse providers for the resources that would be used to treat a typical patient with a given condition and are adjusted for relevant factors that are unique to the patient or provider [65], as opposed to also including a component for profit and risk adjustment [37]. Similarly, the US Department of Veterans Affairs Federal Supply Schedule will be used to value all medications in the societal perspective, as recommended by the Second Panel on Cost Effectiveness in Health and Medicine [37].

Unit cost estimates developed by McCollister et al. [66] will be used to value the resources associated with specific crimes committed. These costs include the direct costs to the criminal justice system (e.g., police-protection, legal and adjudication, and corrections costs), which will be used to inform the state policymaker perspective, as well as societal costs that combine the criminal-justice-system costs with those incurred by victims, both tangible (e.g., medical, property damage or loss, etc.) and intangible (i.e., pain and suffering). Probation officers’ time will be valued according to the mean annual salary and benefit rate reported by the Bureau of Labor Statistics (BLS) [67].

The benefits of work-force participation will be estimated according to the participant’s self-reported wage rate and time spent working. Educational activities will be valued according to self-reported time in school and the estimated return for a year of schooling in the United States [68], applied to the lifetime earnings for individuals in the relevant age range [69]. Participant time costs will be calculated using the self-reported amount of time spent on healthcare-related activities (including travel) and the estimated school or workforce value of the participant’s time [37]. We will use the federal minimum wage to value the time for individuals who are unemployed. If we are able to obtain person-level travel information, including distance traveled and mode of transportation, we will calculate the direct costs of travel accordingly. The cost of public transportation in the area will be used to value the out-of-pocket transportation costs for those using public transit, and IRS standard mileage rates will be used to value transportation costs for those with private transportation. Otherwise, participant transportation costs will be valued according to the average distance traveled by participants, weighted by the proportion who used public transportation versus private transportation, and their respective costs, which will be provided by study staff during site visits.

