We chose to focus on the state policymaker and societal perspectives, as opposed to the healthcare sector perspective for example, because they are particularly relevant for opioid use disorder interventions in this population. However, given the information we are collecting, it will be possible to examine value from other perspectives, if necessary. The state policymaker perspective is crucial to informing resource allocation decisions on behalf of the public, who is primarily responsible for funding prison/jail interventions for substance use disorders, subsequent therapy, and other healthcare for formerly incarcerated persons, as well as the direct costs associated with recidivism. In our prior study of community-dwelling, justice-involved persons with an opioid use disorder, 98% were either on Medicaid or uninsured [40, 41]. The state policymaker perspective will include all study and non-study healthcare costs (e.g., opioid and other substance use disorder therapy; inpatient, outpatient, and ED services; behavioral therapy) paid by Medicaid, and all direct costs to the criminal justice system. In addition to the costs included in the state policymaker perspective, the societal perspective accounts for many of the indirect costs associated with opioid misuse, regardless of who shares the burden [37]; thus, it will also include indirect costs associated with criminal activity (e.g., property damage, pain and suffering, etc.), reduced workplace and school productivity, and those associated with participant time and travel to receive treatment. Not accounting for these indirect costs and the potential value offsets can undermine the true benefit of an intervention. Participant-level costs will be estimated using the resource costing method, which entails weighting each resource unit consumed by a pre-determined unit cost, and summing the values over the relevant time period [37, 38, 42].

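### In the societal costing, an employed participant's hour of care that displaces paid work is charged twice: once as lost work value and again as participant time

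*Protocol article*

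**What the plan says.** Four statements in the protocol article bear on this point.

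- **Components.** Under Methods/Design, Overview, the societal perspective takes the policymaker costs and adds indirect costs, among them "reduced workplace and school productivity, and those associated with participant time and travel to receive treatment". Productivity and participant time are listed as separate items.
- **Work.** In the costing text after Table 2: "The benefits of work-force participation will be estimated according to the participant’s self-reported wage rate and time spent working". The Work row of Table 2 gives the societal source as "Self-reported wages & hours worked" and marks the policymaker perspective as not applicable.
- **Participant time.** In the same paragraph: "Participant time costs will be calculated using the self-reported amount of time spent on healthcare-related activities (including travel) and the estimated school or workforce value". The next sentence reads "We will use the federal minimum wage to value the time for individuals who are unemployed". Table 2 again marks this item as not applicable for the policymaker.
- **Aggregation.** The Analysis section adds the predicted category means within each perspective and carries the totals into the incremental cost-effectiveness ratios (ICERs).

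None of these statements limits participant time to non-working hours or removes care time from the work component.

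**The concern.** Work is valued on time spent working. Read as hours actually worked, an hour of paid work missed for care has already reduced the work benefit by one wage-hour. The participant-time rule covers all reported healthcare and travel time, so it picks up that hour again at a work-based price. Both amounts go into the same societal total.

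The societal incremental cost is then biased against the arm with more care time taken out of paid work. The ICER is the primary outcome of the cost-effectiveness analysis. Two of the four ICERs planned for each of Study A, Study B and the combined analysis are societal. The sensitivity analyses that the article names, on model type and resource prices, would not expose the overlap, because it lies in the quantity being priced. The same overlap can arise for school time, which is also credited as a benefit and can also set the price of participant time.

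**Working it through.** The article gives no figure for this item, so there is nothing to reproduce. The check is an accounting identity.

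**Inputs from the article:** work credited at own wage times time worked; participant time charged on all healthcare and travel hours, at school or workforce value, or at the federal minimum wage if unemployed; categories summed.

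**Inputs not in the article (assumptions):** the share s of care hours that displaces paid work (0 to 1), the hourly wage w, the employment rate e, and the difference in care hours between arms.

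**Cost of one hour of care,** with v the price of participant time:

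- as written: s·w (lost work benefit) + v (time charge)
- each hour counted once: s·w + (1 − s)·v
- overlap: s·v

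**Employed participant, v = w.** The as-written cost is (1 + s)·w and the counted-once cost is w.

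| s | as written | counted once | ratio |
|---|---|---|---|
| 0 | 1.00w | 1.00w | 1.00 |
| 0.10 | 1.10w | 1.00w | 1.10 |
| 0.25 | 1.25w | 1.00w | 1.25 |
| 0.50 | 1.50w | 1.00w | 1.50 |
| 1 | 2.00w | 1.00w | 2.00 |

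**Participant without work.** If the person is out of work for other reasons, s = 0 and the overlap is zero. If care itself is the reason, the second charge is at the minimum wage only. Taking that as 0.6w (an assumption), s = 1 gives 1.60w against 1.00w.

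**Difference between arms, employed participants.** With the same s and w in both arms, the overlap is s × w × (difference in care hours). At assumed wages of $10 to $15, and with s running from 0 to 1:

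- 5 hours: $0 to $75 (1 × $15 × 5)
- 20 hours: $0 to $300 (1 × $15 × 20)
- 160 hours: $0 to $2,400 (1 × $15 × 160)

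**Average over an arm.** Multiply by e. For example, with e = 0.3, s = 0.25, w = $12 and 18 hours (six visits of 3 hours), the overlap is 0.3 × 0.25 × $12 × 18 = $16.20 per participant. All four values are assumptions.

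**The case against.** **A fuller plan may net the two items.** This is a journal article, and the method source it cites for time costs cannot be checked here. That is fair for detail the article leaves open. But the article states the quantity, the price and the summation, and an unseen netting rule would have to change the stated quantity.

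**Displacement is assumed.** The article does not say that care falls in working hours, or whether usual hours or paid leave are reported as time worked. With off-shift care, paid absence or usual hours, nothing is counted twice. This stands, and it is why s must run from 0 and no single size can be given.

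Three stronger readings are tempting and are not supported:

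- *All healthcare time is priced at the participant's own wage.* It is not. The unemployed are priced at the federal minimum wage, and school value is also allowed.
- *In Study B the overlap favours mobile delivery.* Clinic visits may well take longer than visits at the residence, but the Overview asks whether the enhanced arm has more primary and behavioral care alongside less emergency and inpatient care, so the net difference could go either way. The number of injections received is itself an outcome. Table 2 also names only the Non-study Medical and Other Services (NMOS) form as the source for participant time. The Overview includes time spent receiving treatment, but nothing shows that study injection visits are recorded on that form.
- *The error can exceed the $1309 price of an injection.* A full-time worker in a 28-day residential stay (160 work hours at an assumed $12 = $1,920) would reach that, but this is one person at s = 1 with every work hour logged as care. It is not an average difference between arms.

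**Conclusion.** The point holds in limited form. Followed as written, the societal rules charge an employed participant's work-displacing care hour twice, so that a care hour costs 1.0 to 2.0 times the wage as s goes from 0 to 1. This rests on reading time worked as hours actually worked, and on some care falling in paid hours.

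The bias runs against the arm with more work-displacing care time, and the article does not identify that arm. The average effect depends on the employment rate, the displaced share and the difference in care hours, none of which is given. It may be small if few participants work. The state policymaker ICERs are not affected. This is a minor repair to a costing rule and does not threaten the design.

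**What to change.** In the participant-time rule after Table 2, state that time is charged only for healthcare and travel hours not already reflected in reduced work or school time.

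Where the NMOS form cannot separate these hours, report the societal ICERs under two settings: all participant time charged, and no participant time charged for employed participants. For an employed participant's care hour these give (1 + s)·w and s·w, which enclose the counted-once value of w. They bracket each arm's mean cost. They bracket the difference between arms only if s is similar in both, and the report should say so.

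A blanket zero charge for jobholders' inpatient and residential days is not a good substitute. It would drop weekend, off-shift and paid-leave time and so err in the opposite direction.

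The cost is one sentence in the costing rule and one extra sensitivity run, with no new data. The downside is that the lower setting omits some off-hours time of employed participants. According to the Timeline section, Study A's data had not yet been received and Study B was still in progress, so at that point the rule could be set before either cost-effectiveness analysis.

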## Outcomes

The study is comprised of four components, each with its own outcome(s), that culminate in cost-effectiveness analyses. First, we will estimate the cost to the correctional health system of implementing and running each XR-NTX program. Second, we will evaluate differences in the utilization of healthcare services associated with opioid use, across the different arms. Specifically, we will evaluate differences in number of ED, inpatient, primary care, and behavioral healthcare visits. Third, we will evaluate differences in QALYs gained across arms. Finally, we will conduct cost-effectiveness analyses, the primary outcome for which will be the incremental cost-effectiveness ratio (ICER). An ICER is calculated as the incremental cost of a chosen strategy relative to another, divided by the incremental effectiveness of the strategy of interest relative to the other. We will use two measures of effectiveness, one economic, and one clinical. The economic measure of effectiveness will be the QALY. The QALY is an ideal denominator for a cost-effectiveness analysis, as it provides a common measure of effectiveness that permits comparisons across disorders, diseases, and interventions. In addition, generally accepted thresholds for defining value have been established for QALYs, unlike clinical measures [70, 71]. The clinical measure of effectiveness will be *Abstinent Years*, the proportion of the year the individual was abstinent from opioids. Time abstinent is an important measure of effectiveness for clinical stakeholders, and calculating cost-per-*Abstinent*-*Year* enables comparisons with existing economic evaluations that have utilized similar effectiveness measures, especially those that have relied solely on time abstinent measures [7].

## Analysis

The first step of estimating the cost to the correctional health system of implementing and running each XR-NTX program will be to tailor the DATCAP to each setting. Next, we will conduct focused interviews of administrators and staff associated with each treatment strategy across Studies A and B, to ensure that all resources required to implement and continuously manage them, are being captured. The implementation cost will include one-time fixed costs associated with starting the intervention, as well as all monthly fixed and variable costs associated with resources that will be required to manage each treatment strategy on an ongoing basis. Through our interviews, we will estimate the number of patients that could be treated using each strategy on a daily basis, given the current resources, and subsequently calculate the mean costs. The one-time fixed costs associated with starting each strategy will be reported separately; that is, they will not be included in the subsequent economic analyses since they become negligible over time. Research-specific costs will be excluded.

All participant-level data will be analyzed under an intent-to-treat principle, and all analyses will be conducted using a multivariable Generalized Linear Mixed Model (GLMM). The GLMM is an extension of the GLM that allows for the inclusion of random effects. The multivariable aspect of the model is crucial both for the within study comparisons of treatment arms, and the between study comparison of treatment arms, as it allows for the control of factors that are unbalanced between arms because they were not accounted for in the randomization process or may have become unbalanced over time due to loss to follow-up. The GLMM allows one to choose the most appropriate mean and variance functions according to the observed data, and uses all available data for each participant, regardless of whether or not it is complete, making it an ideal statistical procedure for intent-to-treat approaches [38]. Given the differences in mechanisms to generate data, separate multivariable GLMMs will be estimated to predict the mean value for each resource and outcome, at each time period, by study arm. The method of recycled predictions will be used to obtain the final predicted mean values [38]. To account for sampling uncertainty in point estimates, the p-values and standard errors will be estimated using nonparametric bootstrapping techniques within the multivariable framework. All monetary values will be adjusted for inflation.

For Study A ([name], PI) we will model the person period for each 3-month period where detailed assessments are given to participants (i.e., months 3 and 6). For Study B ([name], PI) we will model the person period monthly for the first 7 months and the 5-month follow-up period. By analyzing the relevant person-period for each study, according to when detailed assessments are given to participants, we are able to utilize all observed data from each participant, while accurately identifying and dealing with missing data, and, in addition to the potential confounders discussed above, controlling for differences between arms over time [38.] Next, we will aggregate the monthly values from Study B to align with the 3 and 6 month observation periods of Study B, merge the two datasets, and model the 3- and 6-month person periods.

To better understand the differences in healthcare resource utilization across treatment strategies, we will test for differences in the predicted number of ED, inpatient, primary care, and behavioral healthcare visits between study arms both within- and across-studies over the course of the intervention and follow-up periods, using the methods described above. Similarly, to estimate whether health-related quality-of-life varies across treatment strategies, the predicted health utility index values obtained from the GLMM will be used to estimate QALYs gained using the area under the curve methodology [37, 38, 72], which will then be tested in a similar fashion.

Healthcare services utilized will then be weighted by their respective unit costs and predicted values will be generated. The predicted mean costs for each resource category will be summed and tested according to the relevant perspective, and incorporated into a comprehensive cost-effectiveness analysis along with the predicted outcomes and the average ongoing management costs of each strategy. Four ICERs will be constructed for Study A ([name], PI), Study B ([name], PI), and the combined analysis; i.e., an ICER for each effectiveness measure (QALYs and *Abstinent Years*) and each perspective (state-policymaker and societal). ICER confidence intervals will be estimated using nonparametric bootstrapping techniques within the multivariable framework. Parametric methods based on parameters obtained from bootstrapping will be used to estimate acceptability curves, which illustrate the probability that the intervention is a good value for different willingness-to-pay thresholds (i.e., cost-per-QALY and cost-per-*Abstinent*-*Year*). ICERs will be calculated and acceptability curves will be constructed regardless of the statistical significance for individual cost and effectiveness differences, as the power to detect a difference in costs and effects jointly exceeds the power to do so individually [38].

Sensitivity analyses will be performed to account for uncertainty in assumptions and parameter estimates applied in the analysis [37]. For example, values estimated using the relatively robust and efficient GLMM regression will be compared to those estimated using the more transparent ordinary least squares regression, as well as to the unadjusted mean values. We will also vary the prices of resources, especially the price of the XR-NTX injection, as our prior analyses revealed sensitivity in the cost-effectiveness outcomes around the XR-NTX price [40, 51].

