### Overview of study A ([name], PI): XR-NTX before vs. after reentry

This clinical trial is enrolling 200 persons being released from incarceration who met study admission criteria and expressed interest in XR-NTX treatment. Participants were stratified by sex and sentence requirements for post-reentry criminal justice system contacts (i.e. whether or not required to meet with probation/parole officer) and randomized 1:1 to (a) XR-NTX prior to reentry plus referral to post-reentry treatment, and (b) referral to post-reentry treatment only. Those assigned to the pre-reentry XR-NTX arm receive XR-NTX before reentry with the offer of 3 additional doses of XR-NTX delivered at a community opioid treatment program after reentry. Those assigned to the post-reentry arm are given an appointment to be seen at a community opioid treatment program where they can be admitted within 1–3 days of reentry to receive their first dose of XR-NTX, with the offer of 3 additional doses at the community treatment center. The primary outcome is relapse during the first 3 months after reentry.

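### The power claim behind the joint cost and effect analysis is not generally true, and the bootstrap interval for the ICER loses its meaning when replicates straddle a zero effect difference

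*Protocol article*

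**What the plan says.** Outcomes names the headline quantity of the cost-effectiveness analyses: "the primary outcome for which will be the incremental cost-effectiveness ratio (ICER"). Effectiveness is measured by QALYs and by abstinent years.

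Analysis then makes four statements that bear on this point:

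- Interval for the ratio: "ICER confidence intervals will be estimated using nonparametric bootstrapping techniques within the multivariable framework".
- Second expression of uncertainty: "Parametric methods based on parameters obtained from bootstrapping will be used to estimate acceptability curves", over a range of willingness-to-pay thresholds.
- No significance gate: "ICERs will be calculated and acceptability curves will be constructed regardless of the statistical significance for individual cost and effectiveness differences". The reason given is "as the power to detect a difference in costs and effects jointly exceeds the power to do so individually".
- For the component estimates, "the p-values and standard errors will be estimated using nonparametric bootstrapping techniques within the multivariable framework".

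The article gives no effect size, SD, cost-effect correlation or numerical threshold for the economic outcomes. In a condensed article that is not itself a fault. The direction of the cost difference is left open: Background asks whether the programmes generate downstream savings, and the Methods overview expects more primary and behavioural care but less emergency and inpatient care in the enhanced arm.

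**The concern.** Two separate things are at issue.

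**The power clause.** It is written as a general property of joint analysis. The usual joint quantity is incremental net monetary benefit, INMB = λ·ΔE − ΔC, where λ is the threshold. When ΔE and ΔC are both positive, the cost difference subtracts from the signal while the cost variance still enters the standard error, so the joint comparison can be weaker than the effect comparison alone. A reader who takes the clause at face value would expect the joint analysis to be decisive where the components are not.

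**The ICER interval.** A ratio does not order outcomes once its denominator can change sign. The plan commits to reporting ICERs and their intervals when the effect difference is not significant, which is when replicates are most likely to lie on both sides of zero.

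**Working it through.** The article states no power figure to reproduce, so this is a test of the general statement.

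**Inputs.** From the Study A overview: "This clinical trial is enrolling 200 persons being released from incarceration", "randomized 1:1 to (a) XR-NTX prior to reentry plus referral to post-reentry treatment", hence 100 per arm. From the Study B overview: 180 randomised 1:1, hence 90 per arm. Assumed: two-sided 5% level, no dropout, normal approximation, and all standardised differences d_E, d_C and correlations ρ.

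**Formulas.**
- z_E = d_E·√(n/2), z_C = d_C·√(n/2).
- z_INMB = (r·z_E − z_C) / √(r² + 1 − 2rρ), with r = λ·SD_E/SD_C.
- Power = Φ(|z| − 1.96) + Φ(−|z| − 1.96).

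**1. General bound when the better arm costs more and ρ ≤ 0.** Here z_E and z_C are both positive, so |r·z_E − z_C| is at most the larger of r·z_E and z_C. The denominator is at least √(r² + 1), which is greater than both r and 1. So |z_INMB| is below the larger of z_E and z_C at every threshold, and net-benefit power cannot exceed the larger individual power.

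**2. Illustration.** d_E = 0.3, d_C = 0.15, ρ = 0, n = 100 per arm. Then z_E = 0.3 × 7.071 = 2.121 (power 0.564) and z_C = 0.15 × 7.071 = 1.061 (power 0.186).

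| r | z_INMB | Power |
|---|---|---|
| 1 | (2.121 − 1.061)/√2 = 0.750 | 0.117 |
| 2 | (4.243 − 1.061)/√5 = 1.423 | 0.296 |
| 5 | (10.607 − 1.061)/√26 = 1.872 | 0.465 |

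As r grows, power rises towards 0.564 but does not pass it.

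**3. Cases where the clause holds** (100 per arm).
- Better arm saves money: d_E = 0.3, d_C = −0.3, ρ = 0, r = 1 gives z = 4.243/√2 = 3.000 and power 0.851, against 0.564 for each component.
- Better arm costs slightly more, with positive correlation: d_E = 0.3, d_C = 0.05, ρ = 0.5, r = 2.75 gives z = (5.834 − 0.354)/√5.8125 = 2.273 and power 0.623, against 0.564 and 0.064. For a costlier, better arm, net-benefit power can exceed effect power at some threshold only if z_C < ρ·z_E.

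**4. Other readings of joint power**, with the inputs of step 2. Requiring both components to be significant gives 0.564 × 0.186 = 0.105. A two-degree-of-freedom test against no difference in either has non-centrality 2.121² + 1.061² = 5.625 and power 0.555, just under 0.564. With ρ = −0.5 the non-centrality is (4.5 + 1.125 + 2.25)/0.75 = 10.5 and power is 0.835. So that reading is conditional too.

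**5. Why the ratio interval fails.** Replicates of (ΔE, ΔC) = (+0.01, −$1,000) and (−0.01, +$1,000) both give −$100,000 per QALY. The first is dominant and the second is dominated. At ΔC = $1,000, moving ΔE from +0.001 to −0.001 sends the ratio from +$1,000,000 to −$1,000,000, so near neighbours land at opposite ends of the ordered list.

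**6. When finite limits exist.** The thresholds at which the INMB interval touches zero solve (λΔE − ΔC)² = 1.96²·(λ²s_E² + s_C² − 2λρs_E s_C), where s_E and s_C are the standard errors. The coefficient of λ² is ΔE² − 1.96²s_E², so the set of ICERs is a bounded interval only if the effect difference is itself significant. The chance of that equals the effect power:

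| d_E (assumed) | 100 per arm | 90 per arm |
|---|---|---|
| 0.2 | 0.293 | 0.269 |
| 0.3 | 0.564 | 0.521 |
| 0.4 | 0.807 | 0.765 |
| 0.6 | 0.989 | 0.981 |

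**The case against.** The best defence is that removing the significance gate is sound estimation practice whether or not the power clause is true, so deleting the clause changes no planned analysis. That stands, and it is why the fix leaves the ungated analysis in place. It is also true that the article does not commit to a naive percentile interval, that the full plan may say how replicates crossing zero are handled, and that the cited source may attach conditions to the power statement. But the article asserts the general claim itself and names a bootstrap interval for the ratio; both are stated choices.

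A percentile interval can always be computed. In a simulation with assumed inputs (QALY SD 0.10, cost SD $15,000, cost difference $2,000, zero correlation) its coverage was 0.954 to 0.982. What fails is the meaning of its limits.

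Four stronger readings are tempting, and the document does not support them:

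- *The clause is always false when the better arm costs more.* Step 3 gives a counterexample.
- *The interval is undefined at 90 or 100 per arm.* It depends on the effect difference relative to its standard error, and the article gives neither. At d = 0.6 the problem arises in only 1 to 2% of trials.
- *The primary economic result has no valid measure of uncertainty.* The acceptability curves stay defined when the effect difference is near or below zero, and bootstrap standard errors are planned for the components.
- *A costlier, more effective arm is the expected result.* The article poses the direction of net cost as a question. Nor is a net-benefit power of 5% at a threshold equal to the true ICER a loss of power: it is the type I error where net benefit is exactly zero.

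**Conclusion.** The concern holds in a limited form. The power clause is not generally true on any of the readings tested. For net benefit it cannot hold when the better arm costs more and the cost-effect correlation is zero or negative. The 0.117 to 0.465 against 0.564 illustrates the possible size under assumed inputs; it does not predict the result of either trial.

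The ICER interval is at risk because it is to be reported without regard to significance. Under the normal approximation, the chance of having no bounded interval ranges from 71 to 73% at an assumed d of 0.2 to 19 to 24% at 0.4. The true frequency cannot be derived from the article. The acceptability curves are unaffected, so this is a correction to one justification and one reported interval, not to the whole economic analysis.

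**What to change.** 1. Delete the power clause, or state that joint power may be higher or lower than individual power depending on the sign of the cost difference, the correlation and the threshold. Keep the commitment to calculate ICERs and curves regardless of significance; it does not need the clause.
2. Report incremental net monetary benefit with a bootstrap 95% CI at stated willingness-to-pay thresholds, for both effectiveness measures and both perspectives, beside the ICER point estimate and the planned acceptability curves.
3. Give ICER limits only as the thresholds at which the net-benefit interval crosses zero, and write *no finite limit* where there is none.

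The cost is wording and a few output tables, since the same bootstrap replicates are used. Timeline says the Study A data have yet to be received, so the change can precede the economic analysis. The downside is that some comparisons will be published without finite ICER limits.
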